### Interventions

#### Surgical procedure

In both groups, the subjects are patients without dilated MPD (so-called soft pancreas) and parenchymal atrophy or pancreatitis. There are no regulations regarding the type of disease, the degree of lymph node dissection, portal vein resection or the type of suture used. Patients undergoing pancreaticojejunostomy with duct-to-mucosa anastomosis will be eligible for inclusion; however, there are no regulations regarding the suturing method to approximate the pancreas and the jejunum (Kakita method, two-layer suturing method, modified Blumgart method, etc.). Pancreaticogastrostomy and the invagination method are not permitted.

The MPD diameter will be measured before pancreaticojejunostomy to reconfirm that it is 3 mm or less. If it exceeds 3 mm, the protocol treatment will be terminated. There are no restrictions to the placement of pancreatic stent (yes/no) and the method (external/internal). The presence or absence of a pancreatic stent is registered postoperatively as intraoperative information in the EDC system. Even if the policy of the suturing method to approximate the pancreas and the jejunum is changed during surgery (mattress or non-mattress), the study treatment shall be continued. The anastomotic drains will be placed in all enrolled patients. There are no restrictions to the type and number of anastomotic drains; however, a closed-type drain must be used and must be placed around the pancreaticojejunostomy.

In group B, pancreaticojejunostomy will be performed as already described. In group A, during pancreaticojejunostomy: a 0.3-mm thick PGA felt (Neoveil®; GUNZE, Japan) will be pasted on the ventral side and the dorsal side of pancreatic parenchyma, through which suture between the pancreatic parenchyma and the jejunum will be performed (Fig. 2a); and before abdominal closure (after completion of all reconstruction, after washing in the abdominal cavity), a 0.15-mm-thick PGA felt will be further covered around the anastomotic site and fibrin glue will be sprayed (Fig. 2b).

**Fig. 2 Fig2:**
[figure not shown]
Method using double-coated polyglycolic acid (PGA) felt during pancreaticojejunostomy. **a** A 0.3-mm thick PGA felt (Neoveil®; GUNZE, Japan) will be pasted on the ventral side and the dorsal side of the pancreatic parenchyma. **b** Before abdominal closure, a 0.15-mm thick PGA felt will be further covered around the anastomotic site and fibrin glue will be sprayed

#### Intraoperative photography

To confirm that the surgical procedure is performed correctly by central judgement, intraoperative photographs of the surgical fields will be needed in both groups. The anastomotic site of pancreaticojejunostomy will be photographed with a digital camera immediately after pancreaticojejunostomy (both in groups A and B) and after spraying with fibrin glue (only in group A). Photographs will be sent by email to the administrative office (University of Toyama) within 4 weeks after surgery. Central judgement will be conducted every 6 months for all of the registered patients by the members of the central review committee. If the procedure is not appropriate, the case will be excluded. The central judgement committee has respective members in charge of group A or group B. They will judge to exclude the inappropriate cases from a per-protocol analysis set, and we will review the number of excluded cases in the final report/publication.

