## Background

Partial pancreatoduodenectomy is performed on malignant and benign diseases of the pancreatic head region. The procedure is considered highly difficult and highly invasive. Pancreaticojejunostomy requires a high level of surgical technique for anastomosing the residual pancreas and jejunum. When implementing partial pancreatoduodenectomy, a high-volume centre with highly skilled surgeons is recommended. The incidence of complications after partial pancreatoduodenectomy is reported to be 30–65%, higher than those of other digestive tract surgeries [1–10]. Among these complications, postoperative pancreatic fistula (POPF) is generally recognized as an important complication, because intraabdominal haemorrhage can be fatal. Increases in postoperative hospital stay and surgical mortality rates are also problems.

POPF was first standardized and reported in 2005 [11]. According to the latest International Study Group of Pancreatic Surgery (ISGPS) criteria reported in 2016 [12], the former “grade A POPF” is now redefined and called a “biochemical leak” because it has no clinical importance and is no longer referred to a true pancreatic fistula. Therefore, POPF has only grade B and grade C. Grade B requires a change in the postoperative management; drains are either left in place for > 3 weeks or repositioned through endoscopic or percutaneous procedures. Grade C refers to those POPFs that require reoperation or lead to single or multiple organ failure and/or mortality attributable to the pancreatic fistula.

Pancreaticojejunostomy generally involves a combination of suture between the pancreatic parenchyma and the seromuscular layer of the jejunum, and duct-to-mucosa suture. A clinical study regarding the various kinds of pancreaticojejunostomy was reported for the purpose of lowering the frequency of POPF; nevertheless, the frequency of more than grade B POPF remains approximately 10–20% [13–15]. In soft pancreas patients with unexpanded pancreatic ducts, the risk is further elevated to over 30% [16].

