#### Postoperative management

Blood/ biochemical examination and amylase level measurements of anastomotic drains will be performed on postoperative day (POD) 1 and POD 3. If the amylase level of anastomotic drains on POD 1 is 5000 IU/L or less, we recommend drain removal on POD 4–6. In patients with POPF or infectious signs that require therapeutic drainage, drainage should be continued. Prior to drain removal, a CT/MRI check must be performed to confirm the intra-abdominal situation. After POD 4, blood/biochemical examination or drain amylase-level measurements just before removing the anastomotic drains are performed according to the physician’s discretion. Use of a prophylactic antimicrobial agent after surgery or prophylactic routine exchange of anastomotic drains shall not affect the definition of POPF to be classified. In the case of continued drainage after POD 4–6, we recommend drain removal when either or both of the following conditions continue for 2 consecutive days: the amylase level in the drainage fluid is less than three times the upper limit of institutional normal serum amylase level; or the amount of the drainage fluid is 20 mL/day or less.

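### Photographs used for per-protocol exclusion may arrive 4 weeks after surgery and are judged every 6 months, so the per-protocol set could depend on the outcome; a minor point, cheaply fixed

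*Protocol article*

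**What the plan says.** All of this is in the protocol article.

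- **Intraoperative photography.** The anastomosis is photographed straight after it is completed in both groups, and once more after the fibrin glue in group A only. On transmission: "Photographs will be sent by email to the administrative office (University of Toyama) within 4 weeks after surgery". On review: "Central judgement will be conducted every 6 months for all of the registered patients by the members of the central review committee". On reviewers: "The central judgement committee has respective members in charge of group A or group B". On the consequence: "If the procedure is not appropriate, the case will be excluded", and then "They will judge to exclude the inappropriate cases from a per-protocol analysis set". The number excluded is to be reviewed in the final report.
- **Randomization.** Surgeons cannot be blinded. The outcome assessor is blinded to the procedure.
- **Background.** In the definition of grade B POPF: "drains are either left in place for > 3 weeks or repositioned through endoscopic or percutaneous procedures".
- **Postoperative management.** Drain amylase is measured on postoperative days (POD) 1 and 3. For patients under a stated POD 1 amylase level, "we recommend drain removal on POD 4–6".
- **Statistical analysis plan.** Every analysis is placed on the full analysis set (FAS) under intention to treat.

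**The concern.** A per-protocol set is informative only if membership is settled without regard to outcome. Here the evidence exists on the day of surgery, yet the rule lets an unblinded site hold it until most of the information that defines the primary endpoint is available. The committee can judge only what it receives. If a site has several pictures, the choice among them can be made after the patient's course is known. The judgement itself also comes late, at six-monthly meetings.

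The arms are not symmetric either. Group A needs two photographs and group B one, and each arm has its own reviewers, so any selective effect need not cancel between arms.

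At stake is how the per-protocol comparison can be read. Readers will tend to take it as the effect of felt correctly applied, and that reading fails if leaks help to decide what counts as correctly applied.

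**Working it through.** **Step 1: the timeline.** Days are counted from surgery.

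| Time | Event | Section |
|---|---|---|
| Day 0 | Photographs taken | Intraoperative photography |
| POD 1 and 3 | Drain amylase known | Postoperative management |
| POD 4–6 | Recommended removal window for low POD 1 amylase | Postoperative management |
| After day 21 (3 × 7) | Drain criterion for grade B can be met | Background |
| Day 28 (4 × 7) | Last day to send photographs | Intraoperative photography |
| 3 months | End of complication follow-up | Postoperative follow-up |
| Every 6 months | Central judgement | Intraoperative photography |

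The sending window outlasts the drain criterion by 28 − 21 = 7 days. For the six-monthly review, assume even accrual and judgement at the first meeting after surgery, with 6 months taken as 26 weeks. Then (26 − 4)/26 = 85% of patients are more than 4 weeks past surgery when judged, and about half (3 of 6 months) have finished the 3-month follow-up.

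**Step 2: the plan's own figures.** The point disputes none of them, but they supply the inputs. With 26% v 15.5%, two-sided α = 0.05, 80% power and unpooled variance:

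n = (1.960 + 0.842)² × (0.26 × 0.74 + 0.155 × 0.845) / (0.26 − 0.155)² = 230.2, so 231 per arm as stated. Then 231/0.90 = 256.7, so 257 per arm and 514 in total, as stated.

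**Step 3: what outcome-dependent exclusion could do.** Documented inputs are 231 per arm and the control POPF rate of 26%. Assumed: no true effect (26% in both arms); 5% of group B, and 5% of group A patients without POPF, excluded whatever the outcome; and a share e₁ of group A's POPF cases excluded.

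- Per-protocol rate in A = 0.26(1 − e₁) / [0.26(1 − e₁) + 0.74 × 0.95]
- Patients left in A = 231 × [0.26(1 − e₁) + 0.74 × 0.95]
- Patients left in B = 231 × 0.95 = 219

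The last two columns come from exact enumeration of the two-sided Fisher test at 5%, keeping only significant results in the stated direction.

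| e₁ | Left in A | Rate in A | False benefit | False harm |
|---|---|---|---|---|
| 0% | 222 | 27.0% | 1.1% | 4.0% |
| 5% (unrelated to outcome) | 219 | 26.0% | 1.9% | 1.9% |
| 10% | 216 | 25.0% | 4.1% | 1.1% |
| 20% | 210 | 22.8% | 10.2% | 0.3% |
| 30% | 204 | 20.6% | 24.2% | <0.1% |

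The 0% row is the opposite selection, in which leaked cases are kept more often than others; the bias then runs against the felt. Group A has 231 × 0.26 = 60 POPF cases, so the 10% and 20% rows mean about 6 and 12 of them excluded, against about 3 at the 5% background rate.

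A simpler set-up agrees in pattern. With a normal approximation, 231 per arm and no other exclusions, dropping 5 or 12 POPF cases from group A raises the chance of a false benefit from 2.5% to 6.0% or 17.0%.

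**Step 4: would it show in the report?** In the 30% row the exclusions are 231 − 204 = 27 in A against 231 − 219 = 12 in B, which is visible if counts are given by arm. In the 20% row they are 21 against 12, and in the 10% row 15 against 12, which would pass as chance.

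**The case against.** The strongest reply has five parts.

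1. *The committee decides, not the surgeon, and the images predate any outcome.* This stands. A reader might infer that surgeons choose who is excluded; the article does not say so. What remains is narrower: the committee sees only what is sent, and late choice among images is possible.
2. *No rule says that a missing photograph removes a patient.* This also stands. The article does not say what happens then, and the full protocol may. Withholding a picture therefore cannot be presented as a documented route to exclusion.
3. *The direction is open.* To have a leaked case excluded, a surgeon would have to submit pictures that make the surgeon's own work look wrong. Wanting to show good technique would keep such cases in. A reader might infer that the felt must look better; the documents do not support that.
4. *Four weeks is a latest date.* Photographs may be sent sooner, and complications are followed for 3 months, so status is not always settled by day 28. The site may know the outcome; it cannot be said always to know it.
5. *The result that counts is protected.* All analyses are on the FAS, in a superiority trial where a per-protocol result is supportive, and no per-protocol test is specified. This stands and sets the severity. The sentence "If the procedure is not appropriate, the case will be excluded" names no analysis set and could be read as removing patients from the FAS, but the same paragraph then names the per-protocol set.

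Faster upload alone would also leave the six-monthly review open, since the article does not say whether those reviewers see outcomes. That is why the fix covers both.

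**Conclusion.** The point holds as a minor improvement. The timing rule is stated, it serves no evident purpose for images that exist on day 0, and it lets the input to per-protocol exclusion follow the outcome. The late review adds to this.

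The size of any bias is unknown and its sign is not fixed. The false-benefit figures of 4.1%, 10.2% and 24.2% (against 1.9%) rest on assumed exclusion shares, on selection in group A only, and on a per-protocol Fisher test that the article does not specify. They show sensitivity and are not a forecast.

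The FAS intention-to-treat result is unaffected under every scenario. Nothing in the article suggests that selection is intended, or that the primary conclusion is at risk.

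**What to change.** Amend the photography section as follows.

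- Upload the photographs, time-stamped, to a restricted module of the existing electronic data capture system on the day of surgery or as soon as possible after it, and in any case before POPF is graded.
- Give the central reviewers no postoperative data, whatever the interval between meetings.
- State that a late or missing photograph does not by itself remove a patient from the per-protocol set.
- Report per-protocol exclusions by arm.

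The cost is an upload field, a restricted-access setting and a site instruction. The same pictures are collected, with no added patients or visits, and the system already receives intraoperative information. The downside is some queries about late uploads across 31 centres.

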### Statistical analysis plan

All statistical analyses will be performed using the full analysis set (FAS) under the intention-to-treat principle. The significance level of this test is 5% (two-sided) and the confidence coefficient is 0.95. The Wilcoxon rank-sum test will be used for comparison of continuous variables. The Fisher’s exact test will be used for comparison of categorical variables. Kaplan–Meier curves will be used to represent time-to-event variables, and hazard ratios and 95% confidence intervals will be estimated by the Cox proportional hazard model. *P* < 0.05 will be considered significant.

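### Per-protocol exclusions are judged by different committee members in each arm, with one more photograph in group A and no stated masking to outcome

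*Protocol article*

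**What the plan says.** The Intraoperative photography section of the protocol article sets up a central check of technique. The anastomosis is photographed "immediately after pancreaticojejunostomy (both in groups A and B) and after spraying with fibrin glue (only in group A"), so the first photograph is common to both arms and group A has one more.

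On timing: "Central judgement will be conducted every 6 months for all of the registered patients by the members of the central review committee". On assignment: "The central judgement committee has respective members in charge of group A or group B". On consequence, one sentence names no analysis set: "If the procedure is not appropriate, the case will be excluded". A later sentence in the same section does name one: "They will judge to exclude the inappropriate cases from a per-protocol analysis set". The section also promises that the number of excluded cases will be reviewed in the final report or publication.

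The Statistical analysis plan section says: "All statistical analyses will be performed using the full analysis set (FAS) under the intention-to-treat principle". It gives the per-protocol set no role.

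The Surgical procedure section adds steps for group A only: a 0.3-mm felt placed on the pancreas and sutured through, then a 0.15-mm felt and fibrin glue before closure. For both groups, "there are no regulations regarding the suturing method to approximate the pancreas and the jejunum", although the invagination method is not permitted.

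The blinding paragraph in the Randomization section covers patients, the outcome assessor, physicians, study nurses and statisticians. It does not mention the photograph committee.

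**The concern.** A per-protocol comparison is interpretable only if the rule that removes patients works alike in both arms, or differs for reasons that can be identified. Here three features separate the arms:

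- **Judges.** Each arm has its own members, so the effect of a stricter or more lenient member cannot be separated from the effect of treatment.
- **Opportunities to fail.** Group A can be judged inadequate on felt and glue steps that group B does not have, and it has a further photograph that shows them.
- **Knowledge.** A member assigned to one arm knows the arm. For most cases the fistula status will exist by the time of review, and nothing stated keeps it from the member.

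If excluded group A cases carry a higher fistula risk than the rest, their removal lowers the group A rate in the per-protocol set without any effect of the felt. A per-protocol result more favourable than the FAS result could then be read as support for the device. The count of exclusions alone would not show whether they were related to outcome.

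**Working it through.** **Inputs from the article (Sample size estimation).** Fistula rate 26% without felt and 15.5% with felt, a planned difference of 10.5 points; two-sided α = 0.05; power above 80%; 231 per arm, raised to 257 per arm (514 in total) for about 10% loss.

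**The plan's own figure.** With the unpooled normal formula, n = (1.960 + 0.842)² × (0.26 × 0.74 + 0.155 × 0.845) / 0.105² = 7.849 × 0.3234 / 0.011025 = 230.2, so 231 per arm. Then 231 / 0.90 = 256.7, so 257. Both stated figures reproduce. The pooled formula gives 233.

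**Timing.** Assume even accrual and a review of the preceding 26 weeks of operations. The article's Background describes one route to grade B as a drain left in place for more than 3 weeks. The share of cases past 3 weeks at review is (26 − 3)/26 = 88%. The share past the full 3 months (13 weeks) is (26 − 13)/26 = 50%. So most cases have passed the 3-week point, and about half have completed follow-up.

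**Effect of exclusion in one arm.** The documents give neither an exclusion share nor a fistula rate among excluded cases, so both are assumed and shown as a range. Let p = 0.26 in both arms (no true effect). Remove a share k of group A with fistula rate r, and nobody from group B. The group A per-protocol rate is q = (p − k·r)/(1 − k), and the spurious benefit is p − q = k(r − p)/(1 − k).

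| k (group A only) | r | q | Spurious benefit (points) | Approx. type I error |
|---|---|---|---|---|
| 2% | 40% | 0.252/0.98 = 25.7% | 0.3 | 5.1% |
| 2% | 60% | 0.248/0.98 = 25.3% | 0.7 | 5.4% |
| 5% | 40% | 0.240/0.95 = 25.3% | 0.7 | 5.4% |
| 5% | 60% | 0.230/0.95 = 24.2% | 1.8 | 7.5% |
| 10% | 40% | 0.220/0.90 = 24.4% | 1.6 | 6.8% |
| 10% | 60% | 0.200/0.90 = 22.2% | 3.8 | 16.3% |

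The last column uses 257 patients in group B and 257(1 − k) in group A, with d = p − q, in the two-proportion normal approximation Φ((d − 1.96·se₀)/se) + Φ((−d − 1.96·se₀)/se), where se₀ is pooled and se unpooled. For example, k = 5% and r = 50% give q = 0.235/0.95 = 24.7%, d = 0.0126, se₀ = 0.0389 and se = 0.0389, hence Φ(−1.64) + Φ(−2.29) = 0.051 + 0.011 = 6.2%. The plan's test for categorical variables is Fisher's exact test, which is conservative, so its error rates would be somewhat lower.

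**What reverses or removes the shift.** If r = 26%, the shift is 0 for any k. If both arms lose the same share at the same rate, the shift is also 0. If group B alone lost 5% at a 60% fistula rate, its rate would fall to 24.2% and the felt would look 1.8 points worse.

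**The case against.** The strongest reply is that the main result is insulated. The Statistical analysis plan section puts all analyses on the FAS under intention-to-treat, and the photography section directs these exclusions to the per-protocol set. A reader might infer from "If the procedure is not appropriate, the case will be excluded" that technically inadequate cases leave the primary analysis too. The later sentence in the same section points the other way, so the documents do not support that reading. What remains is loose wording.

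Second, a reader might infer that the per-protocol contrast favours the felt by construction. That is not shown. Both arms are photographed and judged, so group B can lose high-risk cases as well. Nothing in the article says that failed felt applications cluster in high-risk patients, and the shares and rates in the table are assumptions.

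Third, silence on masking is not evidence that reviewers see outcomes, and a committee charter may cover it. This stands in part: masking to outcome may be specified elsewhere. Assignment by arm, however, is stated in the article, and it rules out blinding to arm.

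Fourth, some asymmetry is unavoidable, because only group A has added steps to check. This stands. It does not justify separate judges.

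The promise to report the number of exclusions is a real safeguard, but a limited one: it does not commit to reasons or to the outcomes of excluded cases.

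**Conclusion.** The point holds as a weakness of the per-protocol set. Reviewer strictness is confounded with arm, group A has more stages at which a case can be excluded, and no masking of the committee to outcome is stated. The primary FAS comparison is unaffected provided no case is removed from it.

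The size and direction of any bias cannot be known from the documents. With no true effect, group A exclusions of 2–10% and a fistula rate of 40–60% among them, the spurious benefit is about 0.3–3.8 points against the planned 10.5. These figures assume no exclusions in group B. The lower end is negligible; the upper end needs both a large exclusion share and strongly outcome-related exclusions. The change is worth making because it is cheap and because a supportive analysis of a device, in a trial funded by the company named as the felt's maker, should not invite this question.

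**What to change.** - Have the same committee members judge both arms, against one written criterion per operative step.
- Mask them to the postoperative course, and lock their decisions before outcome data are released.
- Report exclusions by arm, with the step that failed and the fistula status of the excluded cases.
- In the Intraoperative photography section, replace "If the procedure is not appropriate, the case will be excluded" with wording to this effect: *the case is excluded from the per-protocol analysis only and is retained in the FAS*.
- In the Statistical analysis plan section, name the per-protocol analysis as supportive, so that the two sections agree.

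Keep the group A photograph after fibrin glue in the review. Judging both arms only on the shared photograph would not remove the asymmetry, because the first felt is already sutured through by then. It would also keep in the per-protocol set patients who did not receive the full double coating.

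Cost: each member reviews cases from both arms, outcome information must be withheld from the committee, and a few sentences change. Sample size, photographs and surgical procedure stay as they are.
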